## Abstract

**Background:**

Inappropriate fluid administration can impact patient outcome. Intraoperative advanced haemodynamic monitoring coupled with a treatment protocol based on stroke volume optimisation can help determine the appropriate timing for fluid boluses. Although recommended by several anaesthesia societies, this strategy is rarely implemented because protocols are complex and compliance is often poor. The Acumen Assisted Fluid Management (AFM) software is a decision support system that uses machine learning to predict fluid responsiveness and individualise fluid therapy. AFM reportedly predicts fluid responsiveness better than clinicians, decreases preload-dependent states, and improves both macro- and microcirculatory variables. The goal of this international multicentre stepped-wedge cluster randomised trial is to test whether implementing AFM during high-risk surgery improves patient outcome.

**Methods:**

The trial is ongoing in 16 academic hospitals in France, Belgium, Canada, and the USA. All centres (clusters) deliver routine care (control arm) at the start of the study and crossed over (one way) to AFM-guided fluid therapy (intervention arm). The time when different centres switch to AFM is randomised by an independent statistician. At the end of the trial, all centres will cross over to the intervention group. The primary outcome is a composite of major complications and death 30 days after surgery that will be analysed as intention-to-treat. A total of 2000 patients are required to detect a relative 20% differences in the primary outcome between groups.

**Conclusions:**

This trial is powered to provide evidence on whether implementing AFM is effective in reducing postoperative complications in high-risk patients after high-risk abdominal surgery.

**Clinical trial registration:**

NCT06011187.

## Introduction

Among the 313 million major noncardiac surgical procedures performed each year throughout the world, high-risk surgeries account for nearly 80% of perioperative deaths.^1^ Because the underlying cause of death in patients is frequently tissue hypoxemia, maintaining adequate intraoperative cardiac output (CO) and oxygen delivery during surgery may prevent damage to vital organs and decrease morbidity and mortality. Goal-directed stroke volume (SV) optimisation with fluids may improve outcomes in high-risk surgical patients^2^,^3^ and is recommended by several anaesthesiology and professional societies.^4^, ^5^, ^6^ However, despite these recommendations, adoption of this practice has been slow, and few clinicians and institutions currently implement this concept during high-risk surgery.^7^,^8^ One of the reasons is that proposed haemodynamic algorithms are complex and difficult to implement. Moreover, even when these protocols are applied by clinicians, their effectiveness remains limited as only 30% of fluid bolus initiated by anaesthesiologists resulted in appropriate increases in SV.^9^,^10^ This finding could be partly explained by the difficulty for the clinician to sustain attention throughout such high-risk procedures.

To overcome these limitations, a real-time clinical decision support system (The Acumen Assisted Fluid Management [AFM])  was incorporated on the latest version of the Hemosphere monitor (Edwards Lifesciences, Irvine, CA, USA) and was was designed to facilitate SV optimisation during high-risk surgery.^11^, ^12^, ^13^ This software uses machine learning to assess each patient's response to fluids and modifies fluid requirement thresholds to personalise fluid therapy. AFM is associated with decreased preload dependence,^11^ better predict fluid response rates after a fluid challenge,^10^,^13^ improved SV,^12^,^14^,^15^ optimised microcirculatory flow,^14^ and lower arterial lactate.^15^ Its effect on patient outcome, however, remains to be determined.

This international multicentre stepped-wedge cluster randomised trial involving high-risk patients undergoing high-risk abdominal surgery aims to demonstrate that implementing the AFM software (Edwards Lifesciences) can reduce postoperative complications when compared with routine care.

## Methods

The following article adheres to the Standard Protocol Items: Recommendations for Interventional Trials (SPIRIT) statement.^16^ The SPIRIT checklist is provided in Supplemental material 1. The trial sponsor is the Assistance Publique Hopitaux de Paris (APHP); [name] is the head of the project at Paris (APHP) (Direction de la Recherche Clinique et de l’Innovation [DRCI] de l’AP-HP—Pôle Promotion, E-mail: [name]).

### Trial design

The PErsonalized FLuid Administration (PEFLA) trial is an investigator-initiated, international multicentre stepped-wedge cluster randomised controlled trial of 2000 high-risk patients undergoing high-risk abdominal surgery. A stepped-wedge design is a crossover design in which different clusters cross over (i.e. switch treatments) at different time points. The clusters typically cross over in one direction only, from control to intervention. The first time point usually corresponds to a baseline measurement where none of the clusters receive the intervention of interest (Fig 1). At baseline, all the patients will receive usual care. At subsequent time points, clusters will initiate the intervention of interest (i.e. AFM use), and the response to the intervention is measured. More than one cluster may start the intervention at a time point, but the time at which a cluster begins the intervention is randomised. All clusters eventually receive the intervention and the intervention is never removed once it has been implemented. Lastly, the stepped-wedge cluster design decreases the potential for a Hawthorne effect which is a type of reactivity in which individuals modify an aspect of their behaviour in response to their awareness of being observed.

**Figure 1 fig1:**
[figure not shown]
Stepped-wedge study design of the PEFLA trial. Considering the number of participating centres (16 centres) and the duration of this study (24 months), it was proposed to fix eight intervals of 3 months each. The randomisation will involve seven steps, each of them including two to three centres.

### Study setting

This international multicentre trial is currently ongoing in 16 hospitals (12 French, two American, one Belgian, and one Canadian centre). Recruiting centres are hospitals having a high volume of high-risk abdominal surgery, as adapted from the European Society of Cardiology and European Society of Anaesthesiology noncardiac surgery risk score.^17^ It specifically includes major vascular surgery (abdominal aortic aneurysm repair and aorto bifemoral bypass surgery), duodeno-pancreatic surgery, liver resection, bile duct surgery, oesophagectomy, adrenal resection, total cystectomy, cancer debulking, hyperthermic intraperitoneal chemotherapy (HIPEC) surgery, and other types of complex and combined surgery.

### Participants and eligibility criteria

We will include consenting adult patients (aged 18 yr or older) scheduled for elective high-risk abdominal surgery (both open and laparoscopic/robotic assisted) who present at least one of the following comorbidities:•American Society of Anesthesiologists physical status >2•Classification exercise tolerance <4 metabolic equivalents as defined by the guidelines of the American College of Cardiology/American Heart Association•Renal impairment (serum creatinine ≥1.3 mg dl^−1^ or >115 mmol L^−1^ or estimated glomerular filtration rate <90 ml min^−1^ (1.73 m^2^)^−1^ within the past 6 months) or renal replacement therapy•History of coronary artery disease•Chronic heart failure (New York Heart Association Functional Classification ≥II)•Valvular heart disease•Stroke•Peripheral arterial occlusive disease•Chronic obstructive pulmonary disease or pulmonary fibrosis•Diabetes mellitus requiring oral hypoglycaemic agent or insulin•Immunodeficiency because of a disease (e.g. HIV, leukaemia, multiple myeloma, solid organ cancer) or therapy (e.g. immunosuppressants, chemotherapy, radiation, steroids)•Liver cirrhosis (any Child–Pugh class)•Body mass index ≥30 kg/m^2^•Current smoking or 15 pack-year history of smoking

We will not include patients who have cardiac arrhythmias (atrial fibrillation), who cannot give informed consent, who have no affiliation with the French health care system (for the centres in France only), who are participating in another interventional study that may impact the primary outcome, and who are pregnant.

Participants may decide to withdraw from the study at any time and for any reason. Investigators can temporarily or permanently withdraw a participant from the study for any safety reason or if it is in the participant's best interests. If a participant is lost to follow-up (i.e. cannot be located, contacted, or both), investigators will make every effort to reconnect with the participant, document their attempts in the source file, and determine if the patient is still alive. If a participant withdraws consent, any data collected before the date of premature exit may still be used.

### Study interventions

#### Control group: standard of care (as performed today in each centre)

Patients in the control group will receive the standard clinical practice of each centre's anaesthesia department regarding fluid therapy. The standard of care will consequently differ between centres. Some centres use routinely advanced haemodynamic monitoring devices to guide fluid administration, whereas others may not.

#### Intervention group: implementation of the Acumen assisted fluid management software

All patients in the interventional group will be monitored with the Hemosphere haemodynamic monitor (Edwards Lifesciences), which provides in addition to the usual advanced variables (SV, CO, SV variation, and systemic vascular resistance) fluid therapy decision support using the AFM software (Edwards Lifesciences). The AFM software (Edwards Lifesciences) has already been described in detail in previous studies.^13^ Briefly, the main functions of the software are to (1) integrate all monitored haemodynamic variables and continuously analyse a patient's fluid responsiveness; (2) analyse the haemodynamic response to fluid boluses; and (3) predict a patient's current fluid responsiveness and, when appropriate, prompt clinicians to consider a fluid bolus via the monitor's graphical user interface. To be able to do this, AFM uses SV, stroke volume variation (SVV), mean arterial pressure (MAP), heart rate (HR), and systemic vascular resistance (SVR) in two layers to predict fluid responsiveness. The first layer, or population model, uses data from previous populations to predict fluid responsiveness. The second layer, or bolus-log model, evaluates each patient's response to a fluid challenge. This layer will modify the thresholds of SV and other variables to those which are most highly correlated with an individual's fluid responsiveness. This tool thus determines when a patient is fluid responsive and modifies its targets to have the highest probability of predicting fluid responsiveness. In other words, it personalises fluid therapy. To increase compliance, physicians will have a training session before starting inclusion so that they are familiar with the use of AFM. To increase safety, anaesthesiologists will be able to discontinue and modify their haemodynamic strategies and therapies if deemed necessary.

More practically, all patients will have 2–4 ml kg^−1^ h^−1^ of baseline maintenance fluid therapy and additional fluid challenges (100–500 ml) based on the recommendations of the AFM system (Edwards Lifesciences). Ideally, each fluid challenge will be of 250 ml but anaesthesiologists can decide to give 100 ml or 500 ml depending on the clinical situation during the surgery.

#### Relevant concomitant interventions

All components of anaesthesia care will be left at the discretion of the attending anaesthesiologists and institutional guidelines in both groups other than haemodynamic management (fluid therapy) in the AFM group. Mean arterial pressure will be maintained >65 mm Hg during surgery in both groups.

### Primary and secondary outcomes

The primary outcome is a composite of all-cause mortality and major postoperative complications within 30 days after surgery defined as any of the following: acute myocardial injury (including myocardial infarction), acute kidney injury (all stages), severe infectious complications (including deep surgical site infection, pneumonia, sepsis, peritonitis), anastomotic leakage, pulmonary embolism or venous thrombosis, pulmonary oedema, acute respiratory distress syndrome, *de novo* arrhythmia, stroke, reoperation for any cause, non-fatal cardiac arrest, and mortality.

The outcome is met if any of these events occurred. Definitions of these complications are based on recent guideline papers on standard definitions of outcomes in perioperative medicine.^18^, ^19^, ^20^

Secondary outcomes consist of•Incidence of each of the individual components of the composite primary outcome•Incidence of the composite primary outcome within 7 days after surgery•Incidence of a composite of postoperative infection rate within 30 days of surgery. This is defined as one or more of the following infections: surgical site infection, organ space surgical site infection, urinary tract infection, laboratory-confirmed bloodstream infection or infection, source uncertain (this is defined as an infection which could be more than one of the mentioned infections but it is unclear which)•Clavien–Dindo classification and the modified Comprehensive Complication Index scores based on collected outcomes at postoperative day 30•Hospital length of stay•Incidence of unplanned hospital re-admission within 30 days after surgery•Mortality at 90 days after surgery

An outcome adjudication committee will not be used in this trial. All study outcomes will be prospectively assessed by medical doctors or surgeons or intensive care physicians.

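### The secondary 30-day postoperative infection composite is a closed list without pneumonia, so a patient whose only infection is pneumonia is scored infection-free in that outcome

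*Protocol article*

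**What the plan says.** Both infection definitions stand in the protocol article under Primary and secondary outcomes, and both cover the 30 days after surgery.

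- **Primary composite.** One qualifying event is "severe infectious complications (including deep surgical site infection, pneumonia, sepsis, peritonitis"). The word 'including' leaves this list open, and pneumonia is named in it.
- **Secondary infection composite.** The outcome is labelled "Incidence of a composite of postoperative infection rate within 30 days of surgery". Its definition opens with "This is defined as one or more of the following infections" and then lists "surgical site infection, organ space surgical site infection, urinary tract infection, laboratory-confirmed bloodstream infection or infection, source uncertain". The last item is explained as "this is defined as an infection which could be more than one of the mentioned infections but it is unclear which".

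The secondary outcomes also contain "Incidence of each of the individual components of the composite primary outcome", so severe infectious complications are to be reported separately as well.

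**The concern.** The label of the secondary composite is general: it speaks of postoperative infection without limiting the site. A reader of the results will take it as the trial's overall infection rate. The list behind the label leaves out an infection that the primary outcome treats as severe, while it takes in urinary tract infection and surgical site infection without a depth limit, neither of which the primary outcome names.

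Two things are at stake. First, the reported rate will be lower than the label suggests, by the share of patients who have pneumonia and none of the listed infections. Second, the report will carry two 30-day infection results, this composite and the severe-infection component of the primary, which can differ simply because of how they are defined. If AFM-guided fluid therapy changed the frequency of pneumonia in either direction, the severe-infection component could show it. The outcome named postoperative infection could not, except where pneumonia occurs together with a listed infection.

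**Working it through.** The plan gives no figure to reproduce on this point, so the check is a comparison of the two written rules.

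**Step 1: is the secondary list open or closed?** It is closed. The outcome is met by one or more of the items that follow, with no 'including' or 'such as'. The primary's infection item is worded as an open list.

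**Step 2: can pneumonia enter through the source-uncertain item?** No. That item requires an infection that could be more than one of those mentioned. Pneumonia is not mentioned, so a known pneumonia does not qualify.

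**Step 3: does any other part of the article add it?** No. Nothing outside this section adds pneumonia to the composite or explains its absence. The sentence that refers to guideline definitions follows the list of primary complications. The secondary composite then has its own explicit definition.

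**Step 4: apply both rules to example patients.**

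| Only infection(s) within 30 days | Severe-infection item of the primary | Secondary infection composite |
|---|---|---|
| Pneumonia alone | Event | No event |
| Pneumonia with laboratory-confirmed bloodstream infection | Event | Event |
| Pneumonia with urinary tract infection | Event | Event |
| Deep surgical site infection | Event | Event |
| Urinary tract infection alone | Not named; counts only if judged a severe infectious complication | Event |

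The first row is the gap. The second and third rows show why the qualifier matters: pneumonia is lost only when no listed infection accompanies it.

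**Step 5: sepsis and peritonitis.** These are also named in the primary and absent from the secondary list. They may be partly reached through bloodstream and organ-space infection. Pneumonia has no such neighbour on the list.

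**Step 6: size.** The shortfall in the secondary rate, relative to the same list with pneumonia added, is

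shortfall = P(pneumonia) × P(no listed infection, given pneumonia).

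The article gives neither factor, so no number is put in. The finding does not depend on one.

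**The case against.** The strongest reply is that the two outcomes need not nest. They have different names and definitions, and the secondary is wider than the primary in other respects. A patient with pneumonia alone is scored exactly as the stated rule requires. This stands in part: there is no logical contradiction between the outcomes, and misclassification is the wrong word. What remains is a mismatch between an unrestricted label and a narrower list, with nothing in the article to tell the reader of it.

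A second reply is that pneumonia is captured elsewhere. This also stands. It counts in the primary composite at 30 days, in the same composite at 7 days and in the severe-infection component. It can also feed the Clavien–Dindo and modified Comprehensive Complication Index scores, which draw on the collected outcomes. A reader might infer that the trial is blind to an effect on pneumonia; the article does not support that.

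A third reply is that this article condenses a full protocol that is not shown, so the omission may be an abridgement slip or a deliberate choice. That cannot be settled here. But the article does not leave the definition to another document. It states one, and the finding concerns the rule as stated.

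Finally, a reader might infer that the comparison between groups is biased. The same list applies under routine care and under AFM, so the omission does not by itself bias the comparison. It changes which infections the comparison is about.

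**Conclusion.** The point holds for one secondary outcome. As written, the 30-day postoperative infection composite excludes pneumonia, and a patient whose only infection is pneumonia is scored as having none, although the primary outcome counts that same event as a severe infectious complication.

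The consequence is limited. The primary outcome, the sample size and the power are unchanged, and no pneumonia data are lost. The size of the undercount cannot be derived from the documents. Any patient count would rest wholly on an assumed pneumonia rate and an assumed overlap with the listed infections, so none should be used to judge severity.

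It might be tempting to go further and ask that every infection named in the primary be added, or that the depth of surgical site infection be spelled out. The documents do not show a need for either: sepsis and peritonitis may be partly covered already, and surgical site infection is unqualified as it stands.

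The conclusion rests on reading the list as closed and the source-uncertain item as restricted to the listed infections, which is what the wording says.

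**What to change.** Before database lock, and by a documented amendment, do one of the following:

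1. Add pneumonia to the list that defines the secondary infection composite.
2. Keep the list as printed and report beside it a second version that includes pneumonia.
3. If leaving pneumonia out is intended, rename the outcome as non-respiratory infection and state the exclusion.

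The cost is small. Pneumonia is already assessed for the primary outcome, so the first two options should need no new data. Any of the three is nonetheless a change to a pre-specified outcome (its definition, its reporting or its name) in a registered trial that has been recruiting since 1 February 2024, with investigators who are not blinded. The amendment should therefore be dated, give its reason, and be made without reference to results by group. The second option disturbs the pre-specified definition least, because the printed list is still reported.

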### Health economic analysis

We will also conduct a within-trial cost and cost-effectiveness analysis, focusing only on interventions directly evaluated in the trial from the hospital and payer's perspectives. This will be published later as an ancillary substudy of the original one.

### Sample size calculation

On the basis of data from previous published studies from our group, the percentage of patients with at least one major postoperative complication using a standard of care practice varies between 45% and 48.7%. As such, we decided to choose 46.5% as the incidence of postoperative complications in the control group. For a classical randomised trial, 466 patients per group (932 patients in total) are needed to show a 20% relative reduction in the primary outcome (from 45% to 36%), using a power of 80% and (two-tailed) alpha risk of 5%. Of note, the main assumption in randomised controlled trials is that the outcome of an individual patient is completely unrelated to that of any other patient (i.e. they are said to be ‘independent’). This assumption is violated in cluster randomised trials as patients within one cluster (centre in our case) are more likely to respond in a similar manner. A measure of this similarity is known as the intraclass correlation coefficient (ICC). Because of this lack of independence, larger sample sizes are required. The ICC values usually described in the literature and reported by the University of Aberdeen on a database dedicated to ICC (https://www.abdn.ac.uk/hsru/what-we-do/tools/index.php) range between 0.005 and 0.05.

The following criteria must consequently be considered when determining sample size for this study: the randomisation sequence (eight periods for each cluster/centre), time periods (3 months), average number of patients per centre (around 15 patients by period), and the coefficient of variation of cluster size, defined as the ratio of the standard deviation (SD) of cluster sizes. To estimate sample size by considering these additional criteria, Stata (StataCorp, College Station, TX, USA) routine stepped-wedge developed by Hemming and Girling has been used. In our trial, 1680 patients (*n*=840 patients by group) are needed to detect a difference between 46.5% and 36% for an ICC value at 0.01, a two-sided type I error at 5%, and a statistical power greater than 80%. To take into account a possible drop-out rate of at least 16% as 30-day follow-up may be difficult in this population, we will include 2000 patients in total. No planned interim analysis will be conducted during the study.

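### The abstract says 2000 patients are sized for a 20% relative reduction, but the calculation behind that number uses 46.5% to 36%, a 22.6% reduction

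*Protocol article*

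**What the plan says.** The abstract (Methods) states: "A total of 2000 patients are required to detect a relative 20% differences in the primary outcome between groups".

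The section Sample size calculation contains three statements that bear on this:

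- **Control rate.** After citing earlier results between 45% and 48.7%, the authors write "we decided to choose 46.5% as the incidence of postoperative complications in the control group".
- **Individually randomised reference.** "466 patients per group (932 patients in total) are needed to show a 20% relative reduction in the primary outcome (from 45% to 36"%), at 80% power and two-tailed 5% alpha.
- **Stepped-wedge calculation.** "1680 patients (*n*=840 patients by group) are needed", and these "are needed to detect a difference between 46.5% and 36% for an ICC value at 0.01", with "a two-sided type I error at 5%, and a statistical power greater than 80"%. The 1680 is then raised to 2000 for a drop-out of at least 16%.

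The only place where the section calls an effect 20% is the individually randomised reference, where it means 45% to 36%.

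**The concern.** The effect named in the abstract and the effect entered in the calculation differ. When the control rate moved from 45% to 46.5%, the intervention rate stayed at 36%. The difference therefore grew from 9.0 to 10.5 points, and the relative reduction from 20% to 22.6%. A larger effect needs fewer patients, so the sample size is smaller than a 20% target would require.

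This matters when the result is read. The abstract's conclusion calls the trial powered to provide evidence on effectiveness, and the only effect size the abstract gives is 20%. A reader who meets a non-significant result would assume at least 80% power against a 20% reduction.

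The comparison of 932 with 1680 is affected too. It reads as the price of clustering and the stepped-wedge design, but the two numbers belong to different effects.

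**Working it through.** **Inputs from the protocol article.** Control rate 46.5%; intervention rate 36%; 45% to 36% for the reference; 1680 analysed; ICC 0.01 (quoted range 0.005 to 0.05); two-sided 5%; drop-out 16%; 8 periods; around 15 patients per centre and period (all from Sample size calculation). 16 centres and seven steps of two to three centres (Figure 1 legend).

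**Assumptions.** The number of clusters entered in the routine and the coefficient of variation of cluster size are not given. I therefore use several layouts and equal cluster sizes.

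**1. Relative effects**

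- 1 − 36/45 = 20.0%
- 1 − 36/46.5 = 22.6%
- 46.5% × 0.80 = 37.2%

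**2. Individually randomised reference.** Per group, n = [1.96·√(2p̄(1−p̄)) + 0.8416·√(p₁(1−p₁) + p₂(1−p₂))]² / (p₁−p₂)².

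- 45% to 36%: 465.8, so 466 per group and 932 in total, as stated
- 46.5% to 36%: 343.9, so 344 per group and 688 in total
- 46.5% to 37.2%: 440.5, so 441 per group and 882 in total

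**3. Drop-out.** 1680 / (1 − 0.16) = 2000, as stated.

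**4. Stepped-wedge power (Hussey-Hughes model: fixed period effects, random centre effect).**

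Var = I·e·(e + T·τ²) / [(I·U − W)·e + (U² + I·T·U − T·W − I·V)·τ²]

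Here I is the number of clusters and T the number of periods. U is the number of intervention cells, W the sum over periods of the squared number of clusters on intervention, and V the sum over clusters of the squared number of intervention periods. With s² the mean of p(1−p) in the two arms, τ² = 0.01·s² and e = 0.99·s²/m, where m is the number of patients per cell. Power = Φ(difference/SE − 1.96).

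Worked case, two clusters per step: I = 14, T = 8, m = 15, and 14 × 8 × 15 = 1680. U = 56, W = 560, V = 280, so I·U − W = 224 and the second bracket is 3136 + 6272 − 4480 − 3920 = 1008.

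For 46.5% to 36%: s² = (0.248775 + 0.2304)/2 = 0.23959, τ² = 0.002396, e = 0.015813. Var = 14 × 0.015813 × 0.034980 / (3.5421 + 2.4150) = 0.00130, so SE = 0.03605.

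| Effect | Difference / SE | Power |
|---|---|---|
| 46.5% to 36% | 0.105 / 0.03605 = 2.91 | 83% |
| 46.5% to 37.2% | 0.093 / 0.03618 = 2.57 | 73% |
| 45% to 36% | 0.090 / 0.03601 = 2.50 | 71% |

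**5. Sixteen centres, ICC 0.01, different placements of the two three-centre steps**

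| Effect | 1680 analysed | 2000 analysed |
|---|---|---|
| 46.5% to 36% | 82-85% | 87-90% |
| 46.5% to 37.2% | 72-76% | 78-82% |
| 45% to 36% | 69-73% | 76-79% |

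**6. Sensitivity at 1680 analysed.** Over both 20% scenarios and all layouts, power for a 20% reduction is about 73-80% at ICC 0.005 and about 63-68% at ICC 0.05. A cluster-size coefficient of variation of 0.6 lowers power by about 2 points. Cluster autocorrelation between 0.5 and 1 moves it by less than 2 points.

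**The case against.** **The operative calculation is right for its own inputs.** This stands. The sample size section claims more than 80% power for 46.5% to 36%, and that reproduces. It never claims more than 80% stepped-wedge power for a 20% effect. The unsupported statement is the label in the abstract, so the fault is a misnamed effect and not a failed calculation.

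**All 2000 may be analysed.** The Statistical analysis section expects no missing primary outcome data, whereas the sample size section plans for a loss of at least 16%. If nobody is lost, power for a 20% reduction is around 80% (76-82% over both scenarios). The shortfall therefore depends on the planned loss, but 1680 is the number on which the plan bases its own power claim.

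**The relative risk and its confidence interval will show what is excluded.** True: the mislabel changes neither the estimate nor the test. It does change what readers believe the trial was built to detect.

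**A stronger reading that a reader might infer.** Since 16 centres × 8 periods × 15 patients = 1920, one might conclude that the inputs do not give 1680 and that enrolment will fall short. The document does not support this. The figure is only "average number of patients per centre (around 15 patients by period"). Also, 14 × 8 × 15 = 1680 exactly, which fits seven steps of two clusters, and 2000/(16 × 8) = 15.6 agrees with around 15. At most, the number of clusters entered in the routine should be stated.

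**Conclusion.** The point holds as a wrong label on the effect size. The abstract attaches 2000 patients to a 20% relative difference, while the calculation that yields 2000 is for 22.6%.

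At the plan's own analysed number and ICC, a true 20% reduction from the chosen control rate would be missed about 24-28% of the time (power 72-76%), and one from 45% about 27-31% of the time (power 69-73%). Every layout examined at 1680 analysed and ICC 0.01 falls below 80% for a 20% effect. The same model reproduces the plan's claim for 46.5% to 36%, so the shortfall comes from the mismatched rates and not from the choice of model.

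These figures assume an exchangeable centre effect, equal cluster sizes, a normal test and the full 16% loss. One should not infer that 1680 is miscalculated or that the design misses the power stated for the rates in the sample size section.

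**What to change.** Correct the text and leave enrolment unchanged:

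- **Abstract.** Replace the 20% relative difference by 46.5% to 36% (22.6% relative reduction).
- **Sample size calculation.** State that 1680 analysable patients at ICC 0.01 give more than 80% power for 46.5% to 36%, and about 72-76% for a 20% relative reduction from 46.5% (69-73% from 45%).
- **Individually randomised reference.** Put it on the same rates: 344 per group, 688 in total, for 46.5% to 36%.
- **Optional.** State how many clusters were entered in the stepped-wedge routine.

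The cost is a few sentences and a slightly less favourable stated detectable effect. No analysis or trial procedure changes. The correction should be made before the results are read against the 20% target.
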